**Figure 1 F1:**
[figure not shown]
Study design flow chart

### Participants

#### Recruitment

The participants will be recruited from the general population of iPhone users who choose to download ReNeuWell from the Apple Store. The RCT will not happen within a fixed calendar period; rather, prospective participants will be invited to participate in an ongoing manner, whenever they first open the app. All aspects of each condition (such as instructions, activities and educational materials) will be delivered purely via the app. Therefore, participants will not need to interact with another app, a website or any other entity (including the researchers) at any stage of the study. On the ANZCTR registry website, the anticipated date of first participant enrolment is listed as 1 February 2025. Recruitment will continue until the target sample size has been reached.

#### Sample size

The minimum sample size was calculated with the software package G*Power (V.3.1.9.2).^50 51^ The type 1 error rate was set at the conventional level of 0.05. With the desired power of 95% and assuming a correlation of 0.5 between the repeated outcome measures, our calculations determined that a total sample size of 324 participants would be needed to detect a small group-by-time interaction effect (partial η^2^=0.01) with two conditions and two measurement occasions (our study has three measurement occasions, but the second occasion is the primary endpoint of the study, and a power calculation with two occasions is stricter than one with three). However, given that app-based interventions demand relatively low commitment from participants, it is reasonable to assume an attrition rate of at least 50% by the second measurement occasion. Indeed, a recent meta-analysis of RCTs of smartphone interventions^52^ found attrition rates of 53.4% between weeks 9 and 12. Therefore, we set our target sample size at 486 participants, with 243 in each condition.

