#### Statistical analysis

The primary outcomes for this RCT will be the participants’ levels of both mental well-being (as measured by the COMPAS-W) and psychological distress (as measured by the DASS-21). The secondary outcomes will be psychological distress as measured by the K10 and work performance. Potential moderator variables include levels of usage and enjoyment of the app, past mental illness, lifestyle habits, baseline mental health levels and demographic characteristics such as age, sex, education, or occupation.

The initial analyses will be conducted on an intention-to-treat basis and followed by per-protocol analyses. Missing values will be estimated via multiple imputation. The hypotheses will be tested via a linear mixed model estimating the group-by-time interaction effects on the outcome variables. It is hypothesised that levels of mental well-being (COMPAS-W) will increase and levels of psychological distress (DASS-21) will decrease in the training condition relative to the control condition. We will also test for group-by-time interaction effects on work performance and the K10 measure of psychological distress. Any interaction effect may itself be moderated by variables such as age, sex, education, occupation, psychiatric history, lifestyle habits, app usage metrics or baseline mental health levels. Furthermore, we will assess user engagement and retention by computing statistics on the number of participants, the levels of app usage and the levels of attrition relative to the overall number of app downloads. We will also use week 1 and 6 survey responses to examine possible differences between participants who withdraw after these timepoints and those who remain in the study until the week 12 survey, allowing us to interpret our findings with respect to any such differences.

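### The 324 gives 95% power for a 0.40 SD difference in change (interaction partial η²≈0.039); if the stated partial η²=0.01 has its standard meaning, power is about 44%

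*Protocol article*

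**What the plan says.** The Sample size section gives every input to the calculation. On error rate: "The type 1 error rate was set at the conventional level of 0.05". On power and correlation: "With the desired power of 95% and assuming a correlation of 0.5 between the repeated outcome measures". On the result: "a total sample size of 324 participants would be needed to detect a small group-by-time interaction effect (partial η^2^=0.01) with two conditions and two measurement". The calculation thus covers two arms and two time points. The software is named, but not the effect-size convention used in it. No difference is given in SD units or in points on either primary scale.

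The Statistical analysis section makes this interaction the test of the trial's hypotheses: "The hypotheses will be tested via a linear mixed model estimating the group-by-time interaction effects on the outcome variables". The sample-size statement is therefore the power claim for the main analysis.

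**The concern.** For an interaction test, partial η² is normally SS_effect/(SS_effect+SS_error). With two arms and two occasions, the error term is the within-person error, so the correlation between occasions is already inside it. An effect stated this way needs no further adjustment for correlation or number of occasions. If that adjustment is nevertheless applied, the gain from repeated measures is counted twice, and the N obtained belongs to a larger effect than the one printed.

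At stake is how the result will be read. Someone comparing the planned 0.01 with the partial η² reported for the interaction would be comparing two different quantities. They could also take the trial to be well powered for an effect that it would miss more often than find.

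**Working it through.** **Inputs** (Sample size section): α=0.05, power 95%, ρ=0.5, partial η²=0.01, two arms, m=2 occasions, N=324. Allocation is 1:1 (The ReNeuWell app section). The test is a noncentral F with 1 and N−2 degrees of freedom.

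**1. Reproduce the plan's figure.**
- f² = 0.01/0.99 = 0.0101, so f = 0.1005.
- Scale on the raw within-cell variance: λ = f²·N·m/(1−ρ) = f²·N·2/0.5 = 4f²N.
- At N=324, λ = 0.0101 × 324 × 4 = 13.09 and power is 0.9503. At N=322 power is 0.9491.
- The smallest even N is therefore 324, an exact match. The same formula gives 646, 454 and 196 at ρ = 0, 0.3 and 0.7. Entering f=0.10 instead of 0.1005 gives 328.

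**2. What effect that is.** Let δ be the between-arm difference in change and σ the within-cell SD.
- The SD of change is σ·√(2(1−ρ)), which is 1σ at ρ=0.5.
- The test on change scores has λ = δ²N/(4·SD_change²). With SD_change = 1σ, δ = √(4 × 13.09/324) = 0.402 SD. Equivalently, δ = 4f = 4 × 0.1005.
- The interaction test's own partial η² is 4f²/(1+4f²) = 0.0404/1.0404 = 0.039.

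**3. Partial η²=0.01 in its standard sense.**
- λ = f²N, so δ = 2f·√(2(1−ρ)) = 2 × 0.1005 × 1 = 0.201 SD.
- At N=324, λ = 0.0101 × 324 = 3.27.

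| Case | Power for interaction partial η²=0.01 (0.20 SD) |
|---|---|
| 324 analysed, two-occasion group-by-time test | 0.438 |
| 324 analysed, adjusted for baseline at ρ=0.5 | about 0.55 |
| 486 analysed (no attrition) | 0.599 |
| 1,290 analysed | 0.95 |

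**4. Simulation check.** In 20,000 simulated trials with 162 per arm and change scores of SD 1, the rejection rate was 0.951 at δ=0.402 and 0.432 at δ=0.201.

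**5. Context only.** With 243 completers (half of 486), power is about 88% for 0.40 SD and about 34% for 0.20 SD.

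**The case against.** The strongest reply is that nothing was miscalculated. The section lists its inputs and 324 follows from them. It names the correlation as a separate input, which would have no role if partial η² were the interaction test's own. That suggests the effect was scaled on raw variance, and under that convention power is 95% by construction. This stands. A reader might infer that 324 is an arithmetic error, or that the trial simply has 44% power for its stated effect. The document supports neither: the 44% depends on reading partial η² in its standard sense, and the text does not define the term.

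The reply does not rescue the wording. The section attaches an unqualified partial η² to the group-by-time interaction, names no convention, and gives no difference in SD or scale points from which the intended effect could be checked. The 0.40 SD does not depend on the dispute: it follows from 324, 95% power and ρ=0.5 under either reading.

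A second reply is that the planned analysis is a mixed model with three occasions, whereas the 44% is for a two-occasion test. This is fair, and the baseline-adjusted figure of about 55% belongs beside it. Neither approaches 95%. The calculation being checked is itself a two-occasion one aimed at week 6.

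Third, a reader might infer that the investigators intend to treat a null result as ruling out a small benefit. The protocol says no such thing and plans no equivalence or futility conclusion. The risk of misreading is an inference from the power statement, not a stated plan.

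**Conclusion.** The point holds as one about the stated effect size, not about the arithmetic of 324. With 324 analysed and a correlation of 0.5, the design has 95% power for a 0.40 SD between-arm difference in change, an interaction partial η² of about 0.039. That is twice, in SD units, the 0.20 SD that partial η²=0.01 represents in its standard sense. For the latter, power is about 44% (about 55% with baseline adjustment), some 51 points below the stated 95% for the group-by-time test, and 95% power would need about 1,290 analysed.

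The 44% and the 1,290 rest on the standard definition of partial η²; the 0.40 SD does not. All figures assume one outcome at a two-sided 0.05 level and complete data on the stated number. The allowance for attrition is a separate question.

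**What to change.** Keep the sample size and amend the Sample size section in three places:

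1. Name the effect-size convention used in the software.
2. Replace the description of a small interaction with partial η²=0.01 by the effect that 324 analysed participants can detect with 95% power: a between-arm difference in baseline-to-week-6 change of 0.40 SD (interaction partial η²≈0.039 at a correlation of 0.5).
3. Add that power for an interaction partial η² of 0.01 in the standard sense is about 44% with 324 analysed, so a non-significant result does not exclude an effect of that size.

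The new text should say that these figures are for 324 analysed, because the power available to completers depends on the attrition allowance.

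The cost is wording only, here and in the registry entry if it repeats the statement; no extra participants and no change to the analysis. The downside is that the stated detectable effect becomes less favourable.

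### The recruitment target of 486 multiplies 324 by 1.5 instead of dividing by 0.5, so the trial does not have 95% power at its own attrition assumption

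*Protocol article*

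**What the plan says.** All the inputs stand in the Sample size section of the protocol article.

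- Type 1 error: "The type 1 error rate was set at the conventional level of 0.05".
- Power and correlation: "With the desired power of 95% and assuming a correlation of 0.5 between the repeated outcome measures".
- Effect and layout: a partial η² of 0.01 for the group-by-time interaction, "with two conditions and two measurement occasions".
- Result: 324 participants in total.
- Attrition: "it is reasonable to assume an attrition rate of at least 50% by the second measurement occasion". In support, the section says that a meta-analysis of smartphone trials "found attrition rates of 53.4% between weeks 9 and 12".
- Target: "Therefore, we set our target sample size at 486 participants, with 243 in each condition".

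No inflation formula is shown, and no other reason for 486 is given. Three other sections bear on the point. Instructions and timeline makes week 6, the second occasion, the primary endpoint. Recruitment says that enrolment runs until the target is met, with no fixed calendar period. Statistical analysis specifies an intention-to-treat linear mixed model with multiple imputation.

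**The concern.** The target is presented as the consequence of needing 324 participants and expecting to lose at least half. Half of 486 is 243, which is 81 short of 324. The target appears to have been obtained by adding 50% to the required number, which is not the same as allowing for a 50% loss.

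The target also decides when recruitment stops, so the error fixes the size of the trial. If week 6 shows no effect, a reader who relies on this section would judge that result against a 5% chance of missing the planned effect, when the chance is larger.

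**Working it through.** **Step 1. Reproduce 324.** Use the noncentral F test for a within-between interaction, in the form used by G*Power, with the inputs of the Sample size section:

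- f² = 0.01/(1 − 0.01) = 0.010101
- m = 2 occasions, ρ = 0.5, α = 0.05, two groups
- λ = f² × N × m/(1 − ρ) = 0.010101 × N × 4
- degrees of freedom 1 and N − 2

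For N = 324, λ = 13.09 and power = 0.9503. For N = 322, power = 0.9491. The plan's figure of 324 is reproduced exactly, so the inputs have been read as intended.

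**Step 2. Reproduce 486.**

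- 324 × (1 + 0.50) = 486, an exact match.
- 324/(1 − 0.50) = 648, the number to randomise so that 324 remain.
- 324/(1 − 0.534) = 695.3, so 696 in even numbers, at the cited rate.
- 1 − 324/486 = 0.333, the highest attrition at which 486 still leaves 324. The article states this rate nowhere.

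**Step 3. Power that 486 delivers, complete pairs (the plan's own calculation).**

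| Attrition | Participants with week 6 data | λ | Power | Type II error |
|---|---|---|---|---|
| 33.3% | 324 | 13.09 | 95.0% | 5.0% |
| 50% | 243 | 9.82 | 87.7% | 12.3% |
| 53.4% | 226 | 9.13 | 85.3% | 14.7% |

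The type II error is 12.3/5 = 2.5 times the planned value at 50% attrition and 14.7/5 = 2.9 times at 53.4%. With 243 completers, the effect detectable with 95% power is a partial η² of about 0.0133, not 0.01.

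**Step 4. Credit for the baselines of dropouts.** Assume dropout completely at random, ρ = 0.5 and equal variances. In a two-occasion mixed model that uses all 486 baselines, the variance of the interaction, relative to complete pairs only, is (1 − ρ²) + (1 − ρ)² × (share retained), divided by 2(1 − ρ) = 1.

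- 50% attrition: 0.75 + 0.25 × 0.5 = 0.875. λ = 9.82/0.875 = 11.22, power about 92%.
- 53.4% attrition: 0.75 + 0.25 × 0.466 = 0.8665. λ = 9.13/0.8665 = 10.54, power about 90%.

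**Step 5. A baseline-adjusted model.** Adjusting for baseline, or constraining the baseline means to be equal, reduces the relative variance to 1 − ρ² = 0.75.

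- 50% attrition: λ = 9.82/0.75 = 13.09, the value for 324 complete pairs, so power is about 95%.
- 53.4% attrition: λ = 9.13/0.75 = 12.17, power about 94%.

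**The case against.** The arithmetic is hard to dispute, but its consequences can be argued down on four grounds.

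1. *The 88% is for complete pairs, and that is not the planned analysis.* This is fair. The planned mixed model draws on the baselines of dropouts, and Step 4 gives about 92% at 50% attrition. The type II error is then roughly 1.7 times the planned 5% (about twice at 53.4%), not 2.5 to 3 times. Power still falls short of 95%, dropout completely at random is a favourable assumption for an app trial, and the section does not use this argument to justify 486.
2. *The 53.4% belongs to weeks 9 to 12, not week 6.* This also stands: 226, 85.3% and 696 are sensitivity values. The error does not depend on them, because it holds at the 50% that the plan itself assumes for the second occasion. Since the plan says at least 50%, 243 is the most it can expect to retain.
3. *The article attaches 95% to 324 and never says outright that 486 gives 95%.* That is literally so. But the target is introduced as following from the required number and the attrition rate, and no other reading of it is offered.
4. *Power stays above 85% in every case, and neither bias nor type I error is affected.* This is correct and limits the harm. It does not make the stated target follow from the stated inputs.

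**Conclusion.** The concern holds. The target of 486 comes from multiplying by 1.5 where division by 0.5 was needed, and nothing in the article explains it otherwise. At the plan's own 50% attrition, power is 87.7% on the plan's own calculation, about 7 percentage points below the 95% it sets out to achieve. It is about 92% if the mixed model uses all baselines and dropout is completely at random. At 53.4% the corresponding figures are 85.3% and about 90%.

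These results rest on the plan's partial η² of 0.01, correlation of 0.5 and α of 0.05. The shortfall is moderate, but it lies in the number that justifies the trial's size and ends its recruitment, so it must be corrected.

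**What to change.** Correct the Sample size section and the registry entry to state:

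- 486 randomised with 50% attrition leaves 243 at week 6 and gives about 88% power on the completer (G*Power) basis, or about 85% at 53.4% as a sensitivity value. Equivalently, 486 supports 95% power only up to 33% attrition.
- The correct inflation of 324 for 50% attrition is 648.
- If the mixed-model figures (about 92% and 90%) are quoted, they carry the assumption of dropout completely at random.

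This is a change of wording, and its cost is a less favourable power statement.

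Extra enrolment is not required. If the sponsor wants to keep 95% at the present target, a baseline-adjusted primary model, fixed before the data are analysed, gives about 95% with 243 completers when the correlation is 0.5. It gives about 94% at 53.4% attrition, so it does not secure 95% if the loss exceeds half. Raising the target to 648 is the direct alternative. Recruitment has no fixed calendar end, but this would mean 648 − 486 = 162 more participants.

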#### Inclusion criteria

Prospective participants will be informed that participation in the RCT is open to those who are willing to use the app for at least 10 min per day for at least the first 6 weeks of the 12-week study period (and up to 12 weeks), and willing to complete a 10 min survey in weeks 1, 6 and 12. Participants will also need to meet these additional eligibility criteria:

Aged 18 years or older (for informed consent). Able to understand written English (ReNeuWell is currently available in English only), Absence of moderate-to-severe symptoms of mental illness, as measured by a single-item question and scores on the Kessler Psychological Distress Scale—10-item version (K10) screening questionnaire.^53^ Residing in one of the following countries: Australia, New Zealand, the UK, Ireland, the USA, Canada (English-speaking countries). Possesses an iPhone (or iPod Touch) with operating system iOS 14.0 or later (although we intend to release the app on Android devices in the future, pending funding).

When ReNeuWell is first released on the Apple Store, participation in the RCT will be an option only for users residing in Australia. We have approval to recruit participants in all six of the aforementioned countries, but we have decided to confine the study to Australia initially, so that we will be well-positioned (being within our home country) to address any unexpected issues with the app or the trial. Barring any major technical issues or adverse events in this initial period, participation will be extended to the other five countries (and further countries pending future developments).

#### Screening questions

The screening questions ask for the user’s age, whether they understand written English, which country they reside in and whether (yes/no) they currently suffer from a psychological or psychiatric condition. In addition, the screening questions include the K10.^53^ K10 scores of 25 or higher are considered indicative of moderate-to-severe distress and therefore of the respondent being ineligible for study participation. Those who do not pass the screening questions will be redirected to a screen whereby they can continue using the app as a paying user, if they wish. The screening questions (except the K10) are provided in the supplementary materials.

### Survey measures

At each measurement occasion (ie, when the participant first opens the app in weeks 1, 6 and 12), the participants will complete a 10 min survey and will not be able to access further activities until the survey is complete. Each survey comprises a range of questionnaires, but not all measures will be administered at each measurement occasion. Table 2 outlines the questionnaire timings.

**Table 2 T2:** Questionnaires delivered at each timepoint

	Screening (start of week 1)	Survey 1 (start of week 1)	Survey 2 (start of week 6)	Survey 3 (start of week 12)
Screening questions	✓			
K10	✓		✓	✓
Demographics		✓		
Health		✓		
Lifestyle		✓		
COMPAS-W		✓	✓	✓
DASS-21		✓	✓	✓
HPQ		✓	✓	✓
App satisfaction			✓	
Adverse event assessment		✓	✓	✓

COMPAS-W, Composure, Own-worth, Mastery, Positivity, Achievement and Satisfaction for Well-being ; DASS-21, Depression, Anxiety and Stress Scales—21-item version; HPQ, Health and Work Performance Questionnaire; K10, Kessler Psychological Distress Scale—10-item version.

#### K10

K10^53^ will be administered during the initial screening process (as already described) and also at the beginning of the second and third surveys. A moderate-to-high K10 score at the screening stage will make the user ineligible for further participation, with K10 scores again assessed at the second and third survey timepoints. The K10 comprises 10 questions on various symptoms of psychological distress (eg, depression and anxiety symptoms), with a 5-point response scale ranging from *none of the time* to *all of the time*. Respondents are instructed to answer the questions in terms of how they have been feeling *over the past 30 days*. K10 has exhibited acceptable reliability and validity in previous studies, and is one of the most frequently used measures in mental health research and practice.^54–56^

#### Demographics, Health and Lifestyle questionnaires

The Demographics questionnaire will ask about characteristics, including marital status, highest education and current occupation. The Health questionnaire will ask about the user’s psychiatric history, including whether they have been diagnosed with and treated for a mental illness in the past. The Lifestyle questionnaire will ask about the user’s consumption of caffeine, cigarettes and alcohol, as well as their diet, exercise and sleep habits. The Demographics, Health and Lifestyle questionnaires are provided in the supplementary materials.

#### COMPAS-W scale

The COMPAS-W Scale^5^ is a 26-item measure of overall mental well-being and the six subcomponents of Composure, Own-worth, Mastery, Positivity, Achievement and Satisfaction. Each item is a statement with a 5-point response scale ranging from *strongly disagree* to *strongly agree*. The respondents are instructed to answer each statement in terms of how they feel *most of the time* for the week 1 survey, and then how they felt *over the past month* for later timepoints. The COMPAS-W scale has exhibited acceptable reliability and validity in several previous studies.^5 34–37 57^

#### Depression, Anxiety and Stress Scales—21-item Version

The Depression, Anxiety and Stress Scales—21-item version (DASS-21)^58 59^ is a measure of psychological distress (ie, symptoms of depression, anxiety and stress) comprising 21 statements with a 4-point response scale ranging from *did not apply to me at all* to *applied to me very much or most of the time*. The respondents are instructed to answer each statement in terms of how much it has applied to them *over the past week*. The DASS-21 has exhibited acceptable reliability and validity in prior non-clinical research.^60 61^

#### Health and Work Performance Questionnaire scales (employee version)

Two sections from the employee version of the WHO Health and Work Performance Questionnaire^62 63^—scale B9 and scale B12—will be used to measure participants’ work performance. Scale B9 comprises five items asking how many days in the past 4 weeks the respondent missed an entire workday or part of a workday (for health or other reasons), or performed work outside their normal working hours. Scale B12 contains seven items assessing the respondent’s appraisal of their own work performance in the past 4 weeks, with a 5-point response scale ranging from *none of the time* to *all of the time*.

